### Sample size

According to a meta-analysis published in 2013, the average preoperative STAI anxiety score reported in the literature is 43 ± 8. However, this score is 38 + 8 in patients who listen to music prior to surgery compared with patients who receive conventional care alone [1]. Our study hypothesis is that there will be a further decrease of 3 points in the intervention group compared with the control group. This difference will be considered clinically relevant. Furthermore, we posit an intra-individual correlation equal to 0.5 between the measure taken before the music-listening session and the measure taken after the session (conservative assumption). Under this hypothesis, the inclusion of 85 patients in each group (170 in total) will highlight a significant difference in anxiety reduction between the control group (6-point decrease) and the intervention group (9-point decrease), with an alpha level of 5% and a statistical power of 80%.

### Recruitment

The recruitment will take place in the Obstetrics and Gynaecology Department of the University Hospital. The pre-inclusion visit will be performed by physician during the anaesthesia visit between 48 h and 1 month before the inclusion visit corresponding to the day before hospitalisation for surgery. During this pre-inclusion visit, a screening of patients eligible for the study will be carried out. The physician will inform the patient and answer all her questions regarding the objective, the nature of the constraints, the foreseeable risks and the expected benefits of the research. If she wishes to participate, she is asked to create a playlist on the device of her choice, from her own collection to be brought in on the day of hospitalisation for surgery. Each week, 15 to 25 patients are planned for an anaesthesia consultation and may be eligible for inclusion.

## Methods: Assignment of interventions

Eligible patients will be randomised on the day of surgery using EnnovClinical®. Randomisation will be balanced in both groups, single-blinded, with a 1:1 allocation ratio, without stratification. The patient will know her allocation to the control group or to the intervention group, but the care-giver team will be unaware of it. The randomisation list will be established by the statistician from the methodological support department before the start of the research. The method used will be a randomised block approach, using the SAS® Proc Plan. We will build blocks of variable size. The investigator will perform the randomisation directly via the electronic case report form (eCRF) using the CS Random module of the Ennov Clinical® eCRF the day of surgery.

Routine care providers and care team members performing outcome assessment visits will be blinded to the patients’ group allocation. Only the research team will be aware of the group to which patients have been allocated. ‘Do Not Disturb’ signs will be placed on patient room doors during the listening session. Patients will be warned not to mention their group allocations to care providers.

## Methods: Collection, management, and analysis of data

### Data collection method

Data will be collected using an eCRF.

The database will be created by a data manager of the Methodology and Data Management Centre using EnnovClinical® software. Database access will be protected with a user name and password, and will include various safety levels according to role assigned. Research team members will enter the data.

Data-entry agents who are used to working on the eCRF will be responsible for entering the participants’ data. Data-entry and consistency checks will be carried out at the end of the inclusion period by a third party.

### Statistical methods

Qualitative variables will be expressed as absolute numbers and percentages with a confidence interval of 95%. Quantitative variables will be expressed as averages, standard deviations, and ranges if they are normally distributed, and as medians, interquartile ranges, and ranges if they are not. Total sample size will be reported for each analysis. A difference will be considered significant when the *p* critical value is lower than 5%.

#### Primary outcome assessment

Anxiety scores measured after the music-listening session will be compared between the two groups, using an analysis of covariance model (ANCOVA) adjusted to the group and to the anxiety score measured before the music-listening session. This method is recommended for analyses of RCTs that evaluate a variation between an initial value and a post-intervention value.

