### Outcomes

The primary outcome will be the difference between the preoperative anxiety score taken 15 to 20 min before the music-listening session and the preoperative anxiety score taken shortly after the session, as measured with the STAI (State-Trait Anxiety Inventory) for state anxiety [22]. We will use the mean change score from baseline to post music intervention to compare groups. The STAI is a validated and widely used questionnaire for measuring patient anxiety, in particular in the context of music therapy. This self-assessment questionnaire consists of 40 statements, each describing an attitude. It is composed of two separate sections of 20 statements each: The first section assesses trait anxiety and the second measures state anxiety. In each section, ten statements express a negative attitude (e.g. ‘I am worried’) and the other ten express a positive attitude (e.g. ‘I feel calm’). In the section measuring trait anxiety, participants answer each item to report the frequency of their feelings. All items are rated on a Likert-type 4-point scale ranging from ‘almost never’ to ‘sometimes’, ‘often’, and ‘almost always’. In the section measuring state anxiety, participants answer each item to report the intensity of their feelings in the preoperative situation. All items are rated on a Likert-type 4-point scale ranging from ‘not at all’ to ‘somewhat’, ‘moderately so’, and ‘very much so’. STAI results are obtained by adding the scores for negatively worded items and subtracting the scores for positively worded items. Total scores for trait and state anxiety range between 20 and 80: The higher the score, the more the patient is anxious for both types of anxiety. The time needed for the patient to take the test is between 10 and 15 min.

In our study, we will use the validated French version of the STAI (‘Inventaire d’Anxiété Situationnelle et de Trait d’Anxiété’ (IASTA)) [23]. Patients will be asked to fill the first section of the self-assessment questionnaire (trait anxiety) the day before surgery, during the inclusion visit. The day of surgery, they will be asked to fill the second section (state anxiety), which assesses ‘how the individual feels now, at this moment, in terms of concern, tension or nervousness’. A department nurse will administer the questionnaire 15 to 20 min before the start of the music-listening session, and will do so a second time shortly after the session has ended.

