#### Secondary outcomes assessment

Comparisons of VAS values and physiological parameters between the two groups will be performed using the same method as will be used for the primary outcome. Comparisons of immediate post-surgical pain and hospital length of stay between the two groups will be performed using the Student’s *t* test or the Mann-Whitney *U* test, as appropriate.

An intention-to-treat and per-protocol analysis will be conducted. Subgroup analyses considering anxiety, pain, physiological parameters, and length of stay by type of surgery will be performed.

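### Trait anxiety is scheduled before randomisation but named in no analysis in the article; adding it to the primary ANCOVA is a cheap, optional gain in precision

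*Protocol article*

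**What the plan says.** Under Outcomes, the protocol article sets the timing of the trait questionnaire: "Patients will be asked to fill the first section of the self-assessment questionnaire (trait anxiety) the day before surgery, during the inclusion visit". Under Methods: Assignment of interventions, "Eligible patients will be randomised on the day of surgery using EnnovClinical", in variable-size blocks and without stratification. Trait anxiety is therefore due before allocation exists.

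Under Primary outcome assessment, post-session state anxiety is compared "using an analysis of covariance model (ANCOVA) adjusted to the group and to the anxiety score measured before the music-listening session". No other covariate is listed.

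The Secondary outcomes assessment section carries this model over to the VAS and the vital signs (the quote stops one word before the end of the sentence): "Comparisons of VAS values and physiological parameters between the two groups will be performed using the same method as will be used for the primary". Pain and length of stay get a t test or a Mann-Whitney test. The subgroup sentence reads "Subgroup analyses considering anxiety, pain, physiological parameters, and length of stay by type of surgery will be performed". There, anxiety is an outcome and the subgroup factor is type of surgery. Trait anxiety is not among the primary or the four secondary outcomes, the covariates or the subgroup factors. The general descriptive rules under Statistical methods could cover it as a baseline characteristic.

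**The concern.** Patients answer 20 further items on the day before surgery, and the article gives those answers no inferential role. Trait anxiety is a plausible predictor of state anxiety after the session. Because it precedes randomisation, adjusting for it cannot bring in post-randomisation bias. The Discussion itself argues that anxiety should be measured before the session, despite randomisation, to guard against imbalance. The same reasoning extends to a second anxiety baseline that is already being collected.

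What is at stake is precision. Power under the planned model sits almost exactly at 80%, and the Sample size section states no allowance for losses, while the Intervention section withdraws any patient who receives anxiolytic drugs the day before or the day of surgery. A covariate that explains further variance would add some margin without new data collection.

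**Working it through.** **Inputs from the Sample size section**
- SD 8: "the average preoperative STAI anxiety score reported in the literature is 43 ± 8".
- Difference 3 points: "there will be a further decrease of 3 points in the intervention group compared with the control group".
- Pre-post correlation 0.5: "we posit an intra-individual correlation equal to 0.5 between the measure taken before the music-listening session and the measure taken after the session".
- Alpha 5% (taken as two-sided, which the article does not state), power 80%, 85 per group.

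**Step 1: reproduce the planned size**
- ANCOVA residual SD = 8 × √(1 − 0.5²) = 6.928.
- Normal approximation: n = 2 × 6.928² × (1.960 + 0.842)² / 3² = 83.7, so 84 per group.
- With the noncentral t (one covariate, 2n − 3 degrees of freedom) the requirement is 85.
- At 85 per group, the standard error is 6.928 × √(2/85) = 1.063, the noncentrality is 3 / 1.063 = 2.823, and on 167 degrees of freedom power is 80.1%.

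The stated size is thus what the planned ANCOVA needs. A two-sided comparison of change scores has SD 8 × √(2 × (1 − 0.5)) = 8, needs 112 per group by the normal approximation, and does not reproduce 85.

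**Step 2: add trait anxiety**

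Let r be the partial correlation of trait with post-session state, given pre-session state. The residual SD becomes 6.928 × √(1 − r²), with 166 degrees of freedom. The article gives no value of r, so the values below are assumptions.

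| r (assumed) | Variance removed (r²) | Residual SD | Power at 85 per group | n per group for 80% |
|---|---|---|---|---|
| 0 | 0% | 6.928 | 80.1% | 85 |
| 0.1 | 1% | 6.893 | 80.5% | 84 |
| 0.2 | 4% | 6.788 | 81.7% | 82 |
| 0.3 | 9% | 6.609 | 83.7% | 78 |
| 0.4 | 16% | 6.350 | 86.5% | 72 |

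**Step 3: what r might be**

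If trait correlates a with pre-session state and b with post-session state, then r = (b − 0.5a) / √(0.75 × (1 − a²)).
- a = 0.6, b = 0.3 (assumed): the numerator is 0.3 − 0.3 = 0, so r = 0 and power stays at 80.1%.
- a = 0.5, b = 0.5 (assumed): r = 0.25 / 0.75 = 0.33, and power is 84.5%.

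**Step 4: the cost of the extra term**

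With N = 170, chance imbalance in k covariates inflates the expected variance of the group difference by 1 + k/(N − k − 3).
- One covariate: 1 + 1/166 = 1.0060.
- Two covariates: 1 + 2/165 = 1.0121.
- The ratio is 1.0061, about 0.6%. Setting 1 − r² = 1/1.0061 gives a break-even |r| of about 0.08.

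**Step 5: missing trait scores**

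If patients without a trait score were dropped, the gain could vanish. At r = 0.2 with 81 analysed per group (four missing in each, assumed), power is 79.8%. At r = 0.1 with 83 per group it is 79.6%. Both are below the 80.1% of the planned model on all 170.

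**The case against.** The strongest reply is that nothing here is wrong. Adjusting the post-session score for its own baseline is a sound primary analysis, and Step 1 shows that it fits the sample size. This stands, and it sets the severity.

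The size of the benefit is also unknown. Pre-session state is already in the model and carries part of what trait would predict. Excluding patients with a history of anxiety or depression may narrow the range of trait scores and lower r further. This stands too, so the range has to start at zero.

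The trial may have more margin than 80.1% suggests. The Sample size section calls the correlation of 0.5 conservative, and the Abstract gives 170 as a minimum. If the correlation were 0.6 (assumed), the residual SD would be 8 × √(1 − 0.36) = 6.4 and the planned model would have 86.0% power at 85 per group. That weakens the case for urgency but does not make the covariate less useful.

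Three stronger readings are tempting, and the document does not support them:
- A reader might infer that trait anxiety is used nowhere. The article can show only that none of its own analyses names it. A separate SAP may describe it or use it, and the descriptive rules may already cover it.
- A reader might infer that the gain is free. It costs a degree of freedom, a missing-data rule and an amendment, and the gain could be nil.
- A reader might infer that the score will exist for every randomised patient. The article says that patients will be asked to complete it, which makes it scheduled, not guaranteed.

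Finally, enrolment began on 31 July 2017, and the research team both knows the allocation and enters the data. A late change to the primary model therefore needs more protection than a promise made before formal unblinding. That stands and shapes the fix.

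**Conclusion.** The point holds as a low-severity efficiency improvement. Trait anxiety is scheduled before randomisation, no analysis in the article names it, and the primary ANCOVA adjusts only for pre-session state. The planned analysis is valid and correctly sized, and the trial does not need trait to reach 80% power.

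Adding trait would raise power by between nothing and about 6 percentage points (86.5 − 80.1 = 6.4) for an assumed partial correlation of 0 to 0.4. This rests on the protocol's SD of 8, difference of 3 and correlation of 0.5, a two-sided 5% test, and complete data on 85 per group. The downside if trait predicts nothing further is about 0.6% in expected variance.

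**What to change.** In Primary outcome assessment, before anyone looks at data by group, prespecify an ANCOVA of post-session STAI state on group, pre-session STAI state and STAI trait. Keep the model with group and pre-session state alone as a sensitivity analysis.

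State that a missing trait score is imputed from the pooled baseline data, without reference to group or outcome, so that no randomised patient is dropped on its account.

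For the VAS, keep its own pre-session value as the covariate and add trait. STAI state should not replace the VAS baseline.

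No new data are needed. The cost is one degree of freedom, one sentence on missing trait scores, and a written amendment under the Protocol amendments section. The amendment should be dated, so that it can be shown to precede any comparison between groups.

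If the sponsor prefers the present model, that is defensible. A line saying why the trait section is collected would then be enough.

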#### Secondary outcomes assessment

Comparisons of VAS values and physiological parameters between the two groups will be performed using the same method as will be used for the primary outcome. Comparisons of immediate post-surgical pain and hospital length of stay between the two groups will be performed using the Student’s *t* test or the Mann-Whitney *U* test, as appropriate.

An intention-to-treat and per-protocol analysis will be conducted. Subgroup analyses considering anxiety, pain, physiological parameters, and length of stay by type of surgery will be performed.

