### Eligibility criteria

#### Inclusion criteria

Inclusion criteria will be as follows: women aged 18 to 55 years; awaiting scheduled gynaecological surgery under general/local anaesthesia or under sedation; not having received anxiolytic drugs prior to surgery; having a good understanding of French; knowing how to read and write; having signed an informed consent form. To be included in the study, patients will need to have created a personal 20-min playlist for the study.

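### Pain and length of stay are compared without adjusting for type of surgery, which gives up precision that the trial could have at almost no cost

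*Protocol article*

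**What the plan says.** Under Secondary outcomes assessment, the protocol article treats the secondary outcomes in two ways. Anxiety on the VAS and the physiological parameters follow the primary analysis, which is an ANCOVA "adjusted to the group and to the anxiety score measured before the music-listening session". Pain and length of stay get two-sample tests with no covariate: "Comparisons of immediate post-surgical pain and hospital length of stay between the two groups will be performed using the Student’s *t* test". The stated alternative is the Mann-Whitney U test.

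Three other statements bear on this:

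- **Case mix.** The inclusion criteria admit women "awaiting scheduled gynaecological surgery under general/local anaesthesia or under sedation". The exclusion criteria remove emergency and ambulatory operations but do not otherwise restrict the operation.
- **Allocation.** Methods: Assignment of interventions specifies randomisation "with a 1:1 allocation ratio, without stratification".
- **Use of surgery type.** Secondary outcomes assessment adds: "Subgroup analyses considering anxiety, pain, physiological parameters, and length of stay by type of surgery will be performed". This is the only use of surgery type in the analysis.

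**The concern.** Pain is rated 30 minutes after return from the operating room, and length of stay runs from admission to discharge. Neither has a pre-session value, so neither can use the baseline adjustment that the plan applies to anxiety and the physiological parameters. The natural covariate is the operation itself. By planning subgroups on it, the authors show that they expect it to matter and that they will hold the variable.

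An unadjusted test leaves the variation between operations in the error term. The intervals for the music effect are then wider than they need be, and power is lower. The subgroup analyses do not make up for this: they divide 170 patients into smaller sets and give no single adjusted estimate for the whole trial.

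**Working it through.** **Inputs from the protocol article.** 85 per group, 3 points, SD 8, pre-post correlation 0.5, alpha 5%, power 80% (Sample size). All of these concern the STAI. The article gives no SD, effect or power for pain or length of stay.

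**Assumption.** R², the share of outcome variance explained by surgery type. The documents give none, so a range is shown.

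**Step 1: the plan's own figure.** With the ANCOVA standard deviation 8 × √(1 − 0.5²) = 6.928 and a two-sided test, n = 2 × (1.960 + 0.842)² × 6.928² / 3² = 83.7, so 84 per group. With the t distribution, 84 gives 79.7% power and 85 gives 80.1%, so the stated 85 is reproduced. A comparison of change scores or of post-session scores alone (SD 8 in both cases) would need 112 two-sided. The trial size therefore already relies on covariate adjustment for the primary outcome.

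**Step 2: what the unadjusted tests can detect.** At 85 per group and 80% power, the detectable difference is (1.960 + 0.842) × √(2/85) = 0.430 SD. This uses the t-test formula for both outcomes.

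**Step 3: the gain from adjustment.** The residual SD becomes √(1 − R²). The detectable difference is 0.430 × √(1 − R²), and the equivalent unadjusted sample size is 85 / (1 − R²).

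| R² (assumed) | Detectable difference (SD) | Power at 0.430 SD | Equivalent n per group | Gain, 1/(1 − R²) − 1 |
|---|---|---|---|---|
| 0 | 0.430 | 80% | 85 | 0% |
| 0.1 | 0.408 | 84% | 94 | 11% |
| 0.2 | 0.384 | 88% | 106 | 25% |
| 0.3 | 0.360 | 92% | 121 | 43% |

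**Step 4: the price if surgery type explains nothing.** Take five categories, that is, four extra parameters. The lost degrees of freedom alone move power from 80.14% to 80.13%. Chance association between group and category adds a little more: the variance of the group effect is multiplied on average by about (170 − 3)/(170 − 4 − 3) = 167/163 = 1.025. Power at 0.430 SD is then that of 2.802/√1.025 − 1.960 = 0.81 on the normal scale, about 79%. The same factor trims the table slightly: at R² = 0.1 the net gain is 1/(0.9 × 1.025) − 1 = 8%, and at 0.3 it is 39%. Adjustment breaks even at R² = 1 − 163/167 = 2.4%. With fewer categories all these losses shrink.

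**Step 5: is there a validity problem?** Suppose one type of surgery has 30% prevalence and stays 2 days longer (both assumed). The between-group difference in its prevalence has SD √(0.3 × 0.7 × 2/85) = 0.070. A 2-SD imbalance is 14 percentage points and shifts the unadjusted difference by 0.14 × 2 = 0.28 day. The variance due to this type is 0.21 × 2² = 0.84. If that is the whole of R² = 0.2 to 0.3, the total SD is √(0.84/R²) = 2.05 to 1.67 days, and the standard error is SD × √(2/85) = 0.31 to 0.26 day. The shift is then 0.9 to 1.1 standard errors, as 2 × √R² also gives. The unadjusted standard error already allows for imbalance of this kind.

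An illustrative simulation (three surgery types, log-scale outcome, 85 per group, 4000 runs) agrees. Type I error was 4.5 to 5.7% for the t test, the Mann-Whitney test, the adjusted linear model and the van Elteren test. Its R² was about 0.43, above the range used here, so its power figures are not relied on.

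**The case against.** The strongest reply is that nothing planned is wrong. After 1:1 randomisation both tests are valid, the outcomes are secondary, and the trial claims no power for them. This stands, and it limits the point to precision.

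A reader might infer more: that in an unstratified trial a chance excess of major operations in one group could pass for an effect of the music. The documents do not support that as a defect. Step 5 shows that even a 2-SD imbalance moves the estimate by about one standard error for R² of 0.2 to 0.3, and that the planned tests already carry this uncertainty.

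A reader might also infer that anaesthesia type is available for adjustment. It appears in the inclusion criteria only as a description of who is eligible, and nothing shows that it is recorded. Even for surgery type, recording is inferred from the planned subgroups.

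Two further objections stand in part. The size of the gain rests wholly on an assumed R², and excluding emergency and ambulatory surgery may narrow the spread in length of stay. Adjustment also needs a short list of surgery categories, which the article does not give.

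It could be said that covariate adjustment belongs in an analysis plan that is not shown. That answers a complaint of omission, but here the article names the tests outright.

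**Conclusion.** The point holds as an improvement in precision for two secondary outcomes. It does not touch the primary analysis, and it does not make the planned tests invalid or biased. If surgery type explains 10 to 30% of the variance in pain or length of stay, adjustment is worth about 11 to 43% more patients, slightly less once the category parameters are paid for. If it explains nothing, the loss is about one percentage point of power with five categories. The gain depends on the assumed R² and on surgery type being recorded, as the planned subgroups imply. Since adjustment pays once R² exceeds a few percent, the change is worth making.

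**What to change.** Make the main comparison of pain and of length of stay a linear regression on group plus planned surgery type, in a few categories fixed in advance, with robust standard errors. Use the planned operation, so that the covariate is settled before randomisation. Analyse length of stay on the log scale if it is skewed, and decide this before the group codes are known. Report the adjusted difference (or the ratio, on the log scale) with its 95% confidence interval.

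Add anaesthesia type only if it is recorded before randomisation. Keep the unadjusted test, or a van Elteren test stratified by surgery type, as a sensitivity analysis. The van Elteren test gives a p value but not the adjusted difference and interval, so it should not replace the regression.

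The cost is a change of analysis wording and agreement on the surgery categories before unblinding. No patients, visits or changes to randomisation are needed, and no new data item if surgery type is recorded as the subgroup plan implies.
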